## Abstract

**Background:**

Approximately 20–30% of patients with cancer experience a clinically relevant level of emotional distress in response to disease and treatment. This in itself is alarming but it is even more problematic because it is often difficult for physicians and nurses to identify cancer patients who experience clinically relevant levels of anxiety and depression symptoms. This can result in persistent distress and can cause human suffering as well as costs for individuals and to the community.

**Methods:**

Applying a multi-disciplinary and design-oriented approach aimed at attaining new evidence-based knowledge in basic and applied psychosocial oncology, this protocol will evaluate an intervention to be implemented in clinical practice to reduce cancer patient anxiety and depression. A prospective randomized design will be used.

The overarching goal of the intervention is to promote psychosocial health among patients suffering from cancer by means of self-help programmes delivered via an Internet platform. Another goal is to reduce costs for individuals and society, caused by emotional distress in response to cancer.

Following screening to detect levels of patient distress, patients will be randomized to standard care or a stepped care intervention. For patients randomized to the intervention, step 1 will consist of self-help material, a chat forum where participants will be able to communicate with each other, and a Frequently Asked Questions (FAQ) section where they can ask questions and get answers from an expert. Patients in the intervention group who still report symptoms of anxiety or depression after access to step 1 will be offered step 2, which will consist of cognitive behavioral therapy (CBT) administered by a personal therapist. The primary end point of the study is patients’ levels of anxiety and depression, evaluated longitudinally during and after the intervention.

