### The main research questions

#### *Primary research question*

• Do participants who receive Internet-based stepped care report lower levels of anxiety and/or depressive symptoms at 10 months after randomization compared with participants receiving standard care? See details under “Statistical power” below.

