#### *Secondary research questions*

• Will participants who report anxiety and/or depression symptoms at diagnosis and who receive Internet-based stepped care report lower levels of anxiety, depression, post- traumatic stress and improved health-related quality of life in the short and long term (≤24 months after diagnosis)?

• Is Internet-based stepped care cost-effective or at least cost-neutral compared with standard care at 10 and 24 months after diagnosis?

• To what extent do participants use the IS skills and strategies suggested for countering symptoms?

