### Statistical power

The main outcome measure is the Hospital Anxiety and Depression Scale (HADS) [27]. It consists of 14 questions divided into one subscale for anxiety symptoms (seven questions) and one for depressive symptoms (seven questions). Both are 21-point scales. Values <7 points on any of the subscales indicate mild anxiety or depression. Values < 10 points indicate clinically significant levels of anxiety and depressive symptoms. A change of at least 20% on the HADS is considered to be a clinically relevant change [28]. In one previous study of patients with <7 points cut-off on any of the HADS subscales, the mean score for anxiety was 10 and for depression, 8 [6]. To achieve 80% statistical power (alpha = 0.05) needed to detect a mean difference of 2.0 points on the anxiety subscale and 1.6 points on the depression subscale, 65 patients are required in each of the intervention and control groups. Based on experience from previous intervention studies, we estimate that approximately 30% of study participants will not complete the data collection. This means that we need to include at least 95 patients in each group. For the present study, approximately 1,300 patients need to be enrolled, <300 of whom are likely to have anxiety or depression symptoms, <200 of whom can be expected to complete the study.

Patients with <7 points on any of the subscales will be allocated to a reference group and answer questionnaires at baseline and at three observation points during the time of the intervention. They will answer questionnaires that measure anxiety, depression and health-related quality of life.

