### Data collection

All patient-reported data will be collected through the U-CARE platform. Well-known questionnaires with good psychometric properties will be used. Table 1 presents an outline of questionnaires and observation points.

**Table 1 T1:** Summary of the study’s instruments and the observation points at which they will be used

**Instrument**	**Observation points**
HADS	At baseline and at 1, 4, 7, 10, 18 and 24 months
MADRS-S	At baseline and at 10 months
STAI-S	At baseline and at 10 months
ESSI	At baseline
NLEs	At baseline
EROS	At baseline and at 10 months
PCL-C	At baseline and at 10, 18 and 24 months
EORTC QLQ-C30	At baseline and at 1, 4, 7, 10, 18 and 24 months
EORTC QLQ-BR23^1^	At baseline and at 1, 4, 7, 10, 18 and 24 months
EORTC QLQ-PR25^1^	At baseline and at 1, 4, 7, 10, 18 and 24 months
EORTC QLQ-CR29^1^	At baseline and at 1, 4, 7, 10, 18 and 24 months
FACIT-F	At baseline and at 1, 4, 7, 10, 18 and 24 months
ISI	At baseline and at 1, 4, 7, 10, 18 and 24 months
PTGI-SF	At 10 months
Health economic questionnaire	At 1, 4, 7, 10, 18 and 24 months
EQ-5D	At 2 weeks and 1, 4, 7, 10, 18 and 24 months
Patient satisfaction questionnaire	At 1, 4 and 10 months
Internet use questionnaire	At 1, 4, 7, 10, 18 and 24 months
Knowledge and strategies questionnaire	At 2 weeks and 1 and 10 months

*EORTC QLQ* European Organization for Research and Treatment of Cancer (EORTC) Quality of Life Questionnaire, *EQ-5D* Euroqol 5D, *EROS* Environmental Reward Observation Scale, *ESSI* Enriched Social Support Inventory, *FACIT-F* Functional Assessment of Cancer Therapy: Fatigue, *HADS* Hospital Anxiety and Depression Scale, *ISI* Insomnia Severity Index, *MADRS-S* Montgomery-Åsberg Depression Rating Scale – Self-Report, *NLEs* Negative Life Events questionnaire, *PCL-C* Post-Traumatic Stress Disorder (PTSD) Checklist – civilian version, *PTGI-SF* Post-Traumatic Growth Inventory, Short Form, *QLQ-Br25* Quality of Life Questionnaire with diagnosis-specific modules for breast cancer, *QLQ-C30* Quality of Life Questionnaire, Core 30, *QLQ-CR29* Quality of Life Questionnaire with diagnosis-specific modules for colorectal cancer, *QLQ-PR25* Quality of Life Questionnaire with diagnosis-specific modules for prostate cancer, *STAI-S* State-Trait Anxiety Inventory – State anxiety subscale.

^1^ = if appropriate.

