### Data processing and analysis

The end points of the study will be evaluated according to the intention-to-treat principle. In addition the complier average causal effect will be analysed. Differences between the intervention and the control group regarding anxiety, depression, post-traumatic stress, health-related quality of life and the presence and development of these variables over time will be analysed using analysis of variance (ANOVA) with repeated measurements. Should the variables not satisfy the basic assumptions of normal distribution and equal variance, the Mixed regression models will be used for analysis [43]. How and to what extent the different parts of the Internet-based system for psychosocial support are used will be analysed using the data on the study participants’ activities recorded in the system. Qualitative content analysis [44] will be used to analyse the content of the discussion forums and diaries. We also plan to use computerized text analysis. Appropriate methods to control for mass significance will be used.

For process analyses of CBT, multiple regression analysis will be used. The health economic analyses will relate to the interventions’ cost-effectiveness compared with the cost-effectiveness for standard care, which will be analysed in the way that incremental costs are related to the quality-adjusted life years (QALYs). The costs include direct costs (e.g. medical care) and indirect costs (e.g. production) as well as costs for patients, families and health care and to the community. We will analyse the differences between the groups in the short term, after 1, 4, 7, 10 months, and in the long term, after 18 and 24 months. Health economic effects will be analysed after 10 and 24 months. Background variables, such as medical and socio-demographic factors that could potentially function as moderators or confounders, will be controlled for. Internet use other than the IS will be monitored by a project-specific questionnaire administered to both groups in order to control for this potential confounder.

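### The abstract makes the longitudinal course of anxiety and depression primary, the research questions make the 10-month level primary, and the analysis section does not say which result decides

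*Protocol article*

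**What the plan says.** All of the following is in the protocol article.

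- **Abstract, Methods:** "The primary end point of the study is patients’ levels of anxiety and depression, evaluated longitudinally during and after the intervention". No time point is named.
- **Primary research question:** whether stepped-care participants "report lower levels of anxiety and/or depressive symptoms at 10 months after randomization compared with participants receiving standard care". The reader is sent to the Statistical power section for details.
- **Secondary research questions:** whether participants "report lower levels of anxiety, depression, post- traumatic stress and improved health-related quality of life in the short and long term", up to 24 months.
- **Statistical power:** "The main outcome measure is the Hospital Anxiety and Depression Scale (HADS"). The section gives mean differences of 2.0 points (anxiety) and 1.6 points (depression), alpha 0.05, 80% power and 65 patients per group. It gives no time point, SD or sidedness.
- **Data collection, Table 1:** HADS is collected "At baseline and at 1, 4, 7, 10, 18 and 24 months".
- **Data processing and analysis:** group differences and "the presence and development of these variables over time will be analysed using analysis of variance (ANOVA) with repeated measurements", with mixed regression models as the fallback. On timing: "We will analyse the differences between the groups in the short term, after 1, 4, 7, 10 months, and in the long term, after 18". The sentence goes on to include month 24, and month 10 has no special rank in the list.

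**The concern.** The course of HADS over follow-up is what the abstract calls primary and what the research questions call secondary. The analysis section could decide between them but does not. The standard terms of a repeated-measures ANOVA are a group effect averaged over visits and a group-by-time interaction. Neither is the 10-month difference as such.

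The two readings need not agree in this design. Step 2 is offered at 1, 4 or 7 months and lasts 10 weeks, so early visits reflect mainly step 1. A course offered at month 7 and started promptly ends shortly before month 10. An effect that changes over time is therefore plausible, and a contrast over the whole course can succeed where the 10-month contrast fails, or the reverse. If both are in print as primary, whichever succeeds can be reported as the planned one.

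**Working it through.** **1. The statements side by side**

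| Section | Deciding quantity |
|---|---|
| Abstract, Methods | Anxiety and depression followed longitudinally: primary |
| Primary research question | Level at 10 months: primary |
| Secondary research questions | Same symptoms, short and long term: secondary |
| Statistical power | Mean difference, no time point |
| Data processing and analysis | All six visits, none ranked |

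The two research-question sections agree with each other. The abstract sentence departs from them, and the analysis paragraph leaves the matter open.

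**2. Which reading the sample size fits**

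For a two-sided comparison of two means (normal approximation), the standardized difference detectable with 65 per group is

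(1.960 + 0.842) × √(2/65) = 0.491.

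The implied SDs are 2.0/0.491 = 4.07 (anxiety) and 1.6/0.491 = 3.26 (depression). With the t distribution the detectable difference is 0.495. Because no SD is stated, 65 cannot be confirmed independently; it is only consistent with these values. Dropout: 65/(1 − 0.30) = 92.9, so 93, and the stated 95 is adequate (95 × 0.70 = 66.5). No within-patient correlation enters, so the calculation looks like a comparison at one time point, which fits the 10-month question.

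**3. Size of the ambiguity, one subscale**

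Assumptions not in the document: two-sided 0.05; d = 0.495 at full effect; 65 per group at every visit; known variance; equal correlation ρ between any two of the six follow-up visits; and the longitudinal reading taken as the average over those visits.

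Formulas:
- Relative variance of the average: v = (1 + 5ρ)/6, which is 0.417, 0.583 and 0.750 for ρ = 0.3, 0.5 and 0.7.
- Correlation between the two test statistics: √v = 0.645, 0.764, 0.866.
- Noncentrality at month 10: 0.495 × √(65/2) = 2.82, so power = Φ(2.82 − 1.96) = 0.81.
- Noncentrality of the average: 2.82 × (mean of the profile)/√v.

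*No true effect.* Chance that at least one of the two contrasts is significant (simulation, 1,000,000 draws): 0.086, 0.080 and 0.074 for ρ = 0.3, 0.5 and 0.7.

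*True effect, ρ = 0.5.* Profiles are fractions of the full effect at 1, 4, 7, 10, 18 and 24 months:

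| Profile | Mean | Noncentrality of average | Power, month 10 | Power, average | Contrasts disagree |
|---|---|---|---|---|---|
| Constant (all 1) | 1.00 | 3.70 | 81% | 96% | 16% |
| Builds, sustained (0.1, 0.4, 0.7, 1, 1, 1) | 0.70 | 2.59 | 81% | 73% | 18% |
| Builds, fades (0.1, 0.4, 0.7, 1, 0.5, 0.25) | 0.49 | 1.82 | 81% | 44% | 38% |

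Over ρ = 0.3 to 0.7, disagreement runs from 19% to 12% (constant), 17% to 21% (sustained) and 30% to 45% (fading). With a mainly early effect (1, 1, 0.7, 0.4, 0.2, 0.1) at ρ = 0.5, the order reverses: 20% power at month 10 against 55% for the average.

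**The case against.** The strongest defence is that the body of the article already sets the hierarchy. One section is headed as the primary question and names a single time point, the next puts the short and long term under secondary questions, and the sample size fits a single-time comparison. On that view the abstract sentence only describes repeated measurement. The analysis paragraph covers several outcomes at once, and the ranking of contrasts is normally left to an SAP, which is not shown here.

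Much of this stands. The 10-month question is the more specific statement and the natural one to keep. A reader might infer that the two definitions are incompatible. The documents do not support that, because a 10-month contrast can be drawn from a repeated-measures model and the abstract names no average, slope or interaction. The all-visit average used above is one interpretation, not a rule in the plan.

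A reader might also infer much larger error rates, by letting any single visit or an added group-by-time test decide, or a loss of power from splitting alpha over six visits. No section adopts any of these rules. The promise to control for multiple testing names neither a method nor a family, so such figures have no basis in the document.

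What does not stand is treating the abstract as a mere shortening. It assigns primary status to what the secondary questions claim, and the planned ANOVA follows the abstract's wording more closely than the 10-month question. An SAP author could cite either as pre-specified.

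**Conclusion.** The point holds as an inconsistency in the current text about which result is primary. It is not a flaw in the design or the sample size, and N need not change.

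Under the stated assumptions, accepting either contrast raises the type I error from 0.05 to about 0.07 to 0.09 per subscale. How often the contrasts part company depends on a time course that nobody yet knows: at correlation 0.5, about 16 to 18% of trials if the effect is constant or sustained, and about 38% if it peaks at month 10 and fades. The last figure should not be quoted alone. The correlations, profiles and d = 0.495 are all assumed or solved back from 65 per group, and a two-sided test is itself an assumption.

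**What to change.** 1. In the abstract, replace the primary end point sentence with the between-group difference in HADS anxiety and depression at 10 months after randomization, matching the primary research question.
2. In Data processing and analysis, state that the 10-month between-group contrast from the model is the primary analysis for each HADS subscale.
3. In the same section, label the 1, 4, 7, 18 and 24 month differences and the course over time as secondary.

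This is wording only, to be carried into the SAP and fixed before outcome data are seen. It needs no extra patients, visits or data. The small cost is that an effect seen only at another visit, or only on average over time, can no longer be claimed as the primary result. How the two subscales combine at 10 months is a separate matter that this change does not settle.

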**Discussion:**

There is a lack of controlled studies of the psychological and behavioral processes involved in this type of intervention for anxiety and depressive disorders. Since anxiety and depressive symptoms are relatively common in patients with cancer and the availability of adequate support efforts is limited, there is a need to develop evidence-based stepped care for patients with cancer, to be delivered via the Internet.

**Trial registration:**

ClinicalTrials.gov Identifier: NCT01630681

## Background

### The need to identify patients with clinical levels of distress

In Sweden approximately 55,000 persons were diagnosed with cancer in 2010 [1]. Research has shown that a large proportion of patients with cancer have the ability to handle the mental strain that the disease can cause [2-4]. However, 20–30% develop anxiety and depression symptoms [5-7]. There is a need for enhanced psychosocial support for this group in order to prevent persistent psychological distress [8]. Patients with incurable disease report higher levels of anxiety and depression compared with patients who can be cured [9]. Several studies have also shown a correlation between cancer patients’ and their family’s levels of psychological distress [10].

Also, a lack of social network and a low socio-economic status, with a low educational level, low income and unfavourable working conditions, can have a negative impact on cancer patients’ psychological and physical wellbeing as well as on disease progression [11,12]. Such factors should be included as potential moderators in studies of interventions aimed at reducing psychological problems.

### Screening to identify patients needing support

There is a need to identify cancer patients who might need extra psychosocial support. It can be difficult to identify psychological problems as they often manifest in the same way as disease-related symptoms, e.g. with fatigue and impaired functioning. Several screening questionnaires are available to identify patients at risk of developing psychological disorders [13]. General screening of patients may identify patients who have an increased need for psychosocial support and psychological treatment [14]. Internet-based screening may be one way to increase access and automate the calculations that are often necessary when screening for psychiatric disorders. Development of interactive computerized systems and Internet-based research into screening with established instruments is an important part of the methodological development.

### Interactive support and cognitive behavioral therapy

During the last decades, computerized interactive support (IS) efforts that combine health information with support for behaviour change, social support such as discussion forums, and support to make decisions have been developed for patients with chronic diseases. A Cochrane review [15] based on 24 randomized controlled trials in chronic disease concluded that such efforts lead to increased knowledge, positive changes in behaviour, a sense of increased social support, better health, improved functional status and fewer symptoms. The conclusions are that this type of support seems efficient, but more studies are needed to confirm that these results also apply to cancer.

Studies that investigate the effects of web-based discussion forums in which patients share information and discuss experiences show conflicting results. One randomized study concluded that an online discussion forum moderated by health professionals can lead to decreased psychological problems in women with breast cancer [16]. These findings were contradicted by the results of a recently published randomized trial in mixed diagnoses that did not show any positive effects of a non-moderated web-based discussion forum, but rather, a tendency towards poorer psychological wellbeing in the intervention group compared with the control group [17].

Using the Internet to deliver cognitive behavioral therapy (CBT) has many advantages. The Internet has become more integrated into the daily lives of a big part of the population and offers new opportunities for interventions. During the past decade, using Internet-delivered interventions has become more common and, according to a meta-analysis including twelve randomized controlled trials, Internet-based CBT has advantages over traditional CBT for both clients and health care providers’ [18]. The treatment can be obtained at any time and place and participants can use it at their own pace and review the material as often as desired. The level of therapist involvement can be adjusted to the actual need and it may be possible to reduce the therapist time while maintaining efficacy. It may also be possible to reach people through the Internet who might otherwise not receive treatment for their problems. According to the same meta-analysis, studies show that Internet-delivered CBT is as effective as traditional, individual, face-to-face CBT [18]. However, there is need for more, and larger, studies to determine the effects of Internet-based CBT for different types of symptoms in patients with cancer.

There is also a need to understand more about the actual uptake of support. A large proportion of cancer patients with psychological problems do not use available supportive psychosocial resources [19]. According to one study, approximately 30% of patients with cancer who reported symptoms of anxiety or depression declined support [20]. Among the motives reported for refraining from making use of the support offered were a long distance from the clinic and that they already had an established support contact. For patients living a long distance from the clinic, Internet-delivered interventions can be a suitable solution.

### Stepped care, a promising route to more individual uptake of support

Stepped care means that care is given with different intensity for different individuals. Treatment effects are repeatedly evaluated and patients who do not respond to one level of support are transferred to another level and receive more intensive support [21]. Stepped care has successfully been used for treatment of anxiety and depression in the elderly and patients with cancer [22,23]. The initial level of stepped care for psychological problems may comprise education about common symptoms and effective self-help strategies (psycho-education), counselling, and support from other patients. A more intensive treatment level may comprise individual CBT. Stepped care can improve access to support and psychological treatment in a cost-effective manner, particularly if the method is provided via the Internet [18,21,24]. There are virtually no studies of the health economic aspects of interventions aimed at reducing psychological distress in patients with cancer. A few studies suggest that treatment with CBT for anxiety, depression and dysfunctional fear of recurrence of cancer is a cost-effective alternative to other methods of treatment [25,26]. It is important to examine the health economic aspects of this type of intervention to determine whether it is cost-effective to implement in routine care.

